#### Sample size

We aim to detect an effect size of 0.4 standard deviation (SD) in the mean difference in FACIT-Pal total scores (primary outcome) between the two study groups 6 months after baseline. From our pilot data, 0.4 SD is equivalent to a mean difference of 10 points, reflecting a minimal clinically important difference estimated based on 5% of the maximal FACIT-Pal total score [55]. A sample size of 200 patient participants (both groups combined) will give 80% power at a 5% 2-sided type 1 error rate. Accounting for an attrition rate of 34%, typical of studies among patients with advanced cancer [19, 21, 29], we aim to recruit 300 patient participants (150 per group). Correspondingly, up to 300 caregiver participants will be recruited. The criteria to define sample size for implementation outcome interviews will be the point of data saturation where additional interviews do not yield new themes. From previous studies, this is estimated to be around 15 patients, 15 caregivers, and 15 healthcare providers.

### Data analysis

#### Analysis of effectiveness outcomes

Using an intention-to-treat approach, we will compare ENABLE-SG versus usual care at 6 months post-enrolment. Linear regression will be used to compare each patient- and caregiver-reported outcome between intervention and wait-list control groups, with baseline score as a covariate. The negative binomial regression will be used to compare the number of emergency department visits and number of days spent in hospital(s) during the first 6 months post-enrolment, with an offset term that equals 6 months or time from enrolment to death, whichever is earlier. Using a similar approach, we will compare early ENABLE-SG in the intervention group versus delayed ENABLE-SG in the wait-list control group for abovementioned outcomes at 12 months post-enrolment.

We will also assess between-group differences in outcomes from baseline across all timepoints from enrolment using a mixed-effects regression model for repeated measurements. Time since enrolment will be treated as a discrete variable that interacts with the trial groups [56]. Intervention effects will be estimated at each of the 3-monthly timepoints. The comparisons at 3- and 6-months post enrolment will indicate the effect of ENABLE-SG versus usual care; comparisons after 6 months will shed light on the effect of early versus delayed initiation of ENABLE-SG.

For patients, the date of the first specialist palliative care review will be used to compute the following indicators of the timing of palliative care initiation: (1) number of days from enrolment to first palliative care review; (2) number of days from first palliative care review to death. Survival and the timing of palliative care review initiation will be estimated and compared between trial groups using time-to-event analysis.

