### Randomization

After consent is obtained, patient participants will be randomized in a 1:1 ratio to the early ENABLE-SG intervention group or the wait-list control group using randomized permuted blocks generated by an independent statistician. The block size is concealed from the study team until study completion. Randomization will be stratified by tumour types (lung, gastrointestinal, breast, and others) to ensure comparable numbers allocated to both study groups. The consent taker will inform the randomizer after obtaining informed consent and administering baseline questionnaires. The randomizer will then notify the consent taker about the allocation status. The randomizer will not participate in any recruitment procedures.

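### The linear regression for the primary outcome leaves out tumour type, the factor that randomisation is stratified by; the cost is a slightly conservative test, not bias or a loss of the planned power

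*Protocol article*

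**What the plan says.** Under Randomization, the protocol article states that "patient participants will be randomized in a 1:1 ratio to the early ENABLE-SG intervention group or the wait-list control group using randomized permuted blocks", and that "Randomization will be stratified by tumour types (lung, gastrointestinal, breast, and others"), which makes four strata.

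Under Analysis of effectiveness outcomes, the article describes these analyses:

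- **Linear regression** for each patient- and caregiver-reported outcome at 6 months, including the primary FACIT-Pal comparison: "with baseline score as a covariate". A similar approach is to be used at 12 months.
- **Negative binomial regression** for emergency visits and hospital days: "with an offset term that equals 6 months or time from enrolment to death, whichever is earlier". No covariate is named.
- **Mixed-effects model** over all timepoints: "Time since enrolment will be treated as a discrete variable that interacts with the trial groups". Tumour type is not named.
- **Survival and time to palliative care review**: "Survival and the timing of palliative care review initiation will be estimated and compared between trial groups using time-to-event analysis". No test, model or covariate is named.

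Tumour type therefore appears in the allocation scheme and in none of the described models. Only for the linear regression does the article make a covariate choice.

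**The concern.** Permuted blocks within strata hold the two arms close to balance on tumour type, so differences between tumour types add little to the sampling error of the treatment contrast. A model without tumour type does not know this. It leaves those differences in the residual variance and reports a standard error for a looser design than the one used. If tumour type is prognostic, confidence intervals come out wider than they need be, the test rejects under the null less often than 5%, and some attainable power is not used.

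At stake is a modest amount of precision on the primary comparison. There is also a later choice, best closed in advance, between an analysis adjusted for the stratification factor and one that is not.

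**Working it through.** **Inputs from the Sample size section.** "We aim to detect an effect size of 0.4 standard deviation (SD) in the mean difference in FACIT-Pal total scores (primary outcome"); 200 evaluable patients; 80% power; two-sided 5%; 34% attrition; 300 recruited. Since "0.4 SD is equivalent to a mean difference of 10 points", the implied SD is 10/0.4 = 25 points.

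**Inputs assumed, because the documents give neither.** R² is the share of 6-month FACIT-Pal variance left after baseline that tumour type explains: 0, 0.02, 0.05 or 0.10. ρ is the correlation between baseline and 6-month score: 0 or 0.5. Attrition is taken as random.

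**1. Reproduce the plan.** n per arm = 2 × (1.960 + 0.842)² / 0.4² = 98.1, so 99 per arm, or 198 in total. With 100 per arm, power = Φ(0.4/√(2/100) − 1.96) = 80.7%. For recruitment, 200/0.66 = 303 against the stated 300, and 300 × 0.66 = 198. The plan's figures hold. They rest on a plain comparison of two means, with no credit for baseline score or strata.

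**2. Upper bound, with strata perfectly balanced among analysed patients.** The model standard error is too large by 1/√(1 − R²), which is 1.0%, 2.6% and 5.4% at R² = 0.02, 0.05 and 0.10.

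**3. Allow for attrition.** Random loss of 34% brings back part of the imbalance that blocking removed. With a fraction p = 0.66 retained from balanced arms, the variance of the stratum imbalance is 1 − p = 0.34 of its value under simple randomisation. Relative to the model's variance, the true variance is (1 − R²) + 0.34R² = 1 − 0.66R². Hence:

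- standard error too large by 1/√(1 − 0.66R²) − 1
- true type I error = 2 × [1 − Φ(1.96/√(1 − 0.66R²))]
- power without tumour type = Φ((δ − 1.96)/√(1 − 0.66R²))
- power with tumour type = Φ(δ/√(1 − R²) − 1.96)

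Here δ = 2.80 at exactly 80% power with ρ = 0, and 2.80/√(1 − ρ²) otherwise.

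| R² (assumed) | SE too large | True type I error | Power without / with tumour type, ρ = 0 | Gain, ρ = 0 | Gain, ρ = 0.5 |
|---|---|---|---|---|---|
| 0 | 0 | 5.0% | 80.0% / 80.0% | 0 | 0 |
| 0.02 | 0.7% | 4.8% | 80.2% / 80.8% | 0.6 | 0.4 |
| 0.05 | 1.7% | 4.6% | 80.4% / 82.0% | 1.6 | 1.0 |
| 0.10 | 3.5% | 4.3% | 80.8% / 84.0% | 3.2 | 2.0 |

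Gains are in percentage points.

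**4. Check by simulation.** Settings: 300 randomised, blocks of 4 within strata (assumed), stratum shares 30/30/20/20 (assumed), 34% random attrition, 6,000 runs per setting.

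- Type I error of the baseline-only model at ρ = 0: 4.5% at R² = 0.05 and 4.1% at R² = 0.10. The Monte Carlo error is about 0.3 points.
- Power without / with tumour type at ρ = 0: 80.0% / 81.6% at R² = 0.05, and 79.8% / 83.2% at R² = 0.10.
- Power at ρ = 0.5: 89.5% / 90.9% at R² = 0.05, and 90.4% / 92.3% at R² = 0.10.

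These agree with the table within simulation error.

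**The case against.** The strongest reply is that the article is condensed and that covariate lists commonly sit in an analysis plan, which is not shown here. For the negative binomial, mixed and time-to-event analyses this stands: the article is silent on tumour type there, and silence is not an error. For the linear regression it stands only in part. The article does not say its list is complete, but it names one covariate for the primary comparison and passes over the factor used for randomisation.

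A reader might draw four stronger conclusions, none of which the documents support.

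- **The trial loses its planned power.** It does not. The sample size takes no credit for baseline or strata, so the baseline-only model stays at about 80% when ρ = 0 and near 90% when ρ = 0.5. What is given up is a possible gain above target.
- **The result is biased or the error rate inflated.** Neither follows. The linear estimate is unbiased with or without tumour type, and the test errs on the conservative side.
- **The survival comparison is unstratified and its hazard ratio pulled towards 1.** The article writes no such model; it says only that time-to-event methods will be used. It also gives no figure for how strongly tumour type predicts survival.
- **The same mechanism applies in full to caregivers.** They take the patient's group, and a patient may enrol without one. Blocking patients does not guarantee balance on tumour type among enrolled caregivers, so the argument is weaker there.

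The perfect-balance figures in step 2 also overstate the effect, because the article itself plans for 34% attrition.

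**Conclusion.** The mismatch is real for the patient linear models, and its direction is certain if tumour type is prognostic beyond baseline. Its size is small and conditional: over an assumed R² of 0.02 to 0.10, the standard error is roughly 1% to 3.5% too large, and about 0.6 to 3 power points could be gained. The gain is smaller when baseline predicts outcome well, and zero when tumour type adds nothing. These figures rest on random attrition of 34% and on an R² that the documents do not give. This is a low-cost improvement, not a flaw that threatens the trial's conclusion. If an analysis plan already includes tumour type, confirming that closes the point.

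**What to change.** In the linear regression for patient-reported outcomes at 6 and 12 months, add the four-level tumour type as a fixed covariate beside the baseline score, or state why it is left out. Carry the same factor into the mixed and negative binomial models for patients, and use it as a stratification factor in the survival and time-to-review analyses, where the article names no covariates. For caregivers, the patient's stratum can be added for consistency, without claiming that blocking has balanced it.

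The change costs one line of wording and three degrees of freedom (four levels less one). The variable is already recorded for randomisation. It should be fixed before outcomes are seen by group.

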#### Analysis of implementation outcomes

Transcribed interviews will be analysed using a thematic analysis approach guided by the CFIR [54]. The study team will familiarize themselves with the data and context before performing deductive coding according to the CFIR framework. Passages will also be open-coded inductively to form code categories. Code categories will be systematically compared against one another to determine mutual exclusivity, clustering, or connectivity between categories. The dimensions and properties of concepts will then be developed. This process will repeat until patterns or themes emerge. Data will be coded independently by at least two coders to enhance the credibility of constructs derived from analyses. Regular team meetings will be conducted to resolve disagreements, document reflexive notes, and discuss interim findings.

Descriptive statistics will be used to describe responses from the structured feedback survey and data on fidelity. Counts and percentages will be used to summarize categorical variables. Mean and SD or median and interquartile range will be used to summarize normally distributed and non-normally distributed continuous variables, respectively. Additionally, for modified ENABLE-SG sessions, a narrative recount of what was modified, the underlying rationale, and the content will be presented. To assess penetration, the approach-to-participation rate will be tabulated at the oncologist level.

Implementation costs of ENABLE-SG will be captured prospectively using an activity-based costing approach. Non-sunk implementation costs will be combined with any potential cost offsets from improved health and used as the numerator in a cost-effectiveness analysis (CEA) from the health system perspective. The denominator of the CEA will focus on quality-adjusted life years (QALYs) gained, accounting for both differences in survival and health-related QoL resulting from ENABLE-SG. Survival differences will be estimated using time-to-event (death) analysis. QALY differences will be computed using EQ-5D-5L data at baseline, 3-, and 6-months post-enrolment. The resulting incremental cost-effectiveness ratio (ICER) will be compared to established thresholds for cost-effectiveness. One-way and probabilistic sensitivity analyses will also be constructed to gauge the variability of the results and the influence of select parameters and assumptions (e.g., survival duration, QoL benefits 6 months post-intervention).

### Ethics and dissemination

This study received ethical approval from the SingHealth Centralized Institutional Review Board (CIRB 2023/2462). Informed consent will be obtained from all participants. No formal monitoring committee was formed. The study team, led by the Principal Investigator, will be responsible for data monitoring to ensure data integrity, accuracy, and confidentiality. Secure databases will be used (REDCap, institutional database). All study data will only be accessible to authorized research personnel. All amendments reflecting study modifications will be submitted for institutional review board approval. The principal investigator declares no competing interests for the overall trial. We will present study results at national and international scientific meetings, publish them in peer-reviewed journals, and deposit the publication(s) in our institution’s open access repository within 12 months of publication. Authorship eligibility will abide by International Committee of Medical Journal Editors recommendations.

## Discussion

This study evaluates the effectiveness and implementation of a culturally adapted and piloted health coaching model (ENABLE-SG) as an early palliative care intervention for patients with advanced cancer and their caregivers. The ENABLE-SG model addresses existing gaps in current models of palliative care. First, early integration of palliative care in the patient's disease trajectory reverses the trend of palliative care being delivered late in the last weeks of life. Second, a proactive care approach shifts away from the current reactionary illness-stress paradigm, allowing patients to take charge of their health. By proactively equipping patients and caregivers with self-management skills, we anticipate that ENABLE-SG empowers them to cope better while living in the community, leading to better QoL and possibly lower acute healthcare utilization.

This study will generate evidence on the value of early palliative care provision on patient and caregiver outcomes and outline ways to support widespread ENABLE-SG implementation or its modification if needed. At the individual level, ENABLE-SG may facilitate a better coordinated and patient-centred approach to delivering supportive and palliative care to patients with advanced cancer and their caregivers. At the organizational level, insights into implementation processes will inform future upscaling and dissemination of this early palliative care model and bolster support for employing non-specialist, trained health coaches to deliver palliative care sustainably. Collectively, study findings may inform healthcare policy to promote early access to palliative care.

The study has several strengths. First, a wait-list control design represents a resource-efficient approach to investigating the impact of ENABLE-SG based on its contents and the timing of introduction. The 6-month wait-list duration is appropriate given that the median survival in the Singapore setting is 1.3 years in adults with stage 4 cancer and > 4 years in adults with stage 3 cancer. Second, the hybrid effectiveness-implementation design facilitates data collection from real-world settings to generate insights on factors influencing successful implementation in outpatient oncology clinics. Third, by primarily delivering the health coaching sessions over the phone, this study evaluates early palliative care provision through a telehealth delivery mode that is readily scalable in a lean healthcare system workforce.

## Conclusion

This hybrid type 1 effectiveness-implementation study evaluating the ENABLE-SG model aims to change how palliative care is provided – from a reactive illness approach to a proactive wellness paradigm. This proactive approach of empowering patients and their caregivers with self-management skills can reap long-term benefits for a broader spectrum of advanced illnesses beyond cancer. Moreover, insights into implementation processes can facilitate model expansion to benefit more patients and caregivers.

## Data Availability

No datasets were generated or analysed during the current study.

## Abbreviations

Brief-COPE: Brief Coping Orientation to Problems Experienced
CES-D: Centre for Epidemiological Studies-Depression
CIRB: Centralized Institutional Review Board
CFIR: Consolidated Framework for Implementation Research
ENABLE: Educate, Nurture, Advise, Before Life Ends
ENABLE-SG: Educate, Nurture, Advise, Before Life Ends for Singapore
EQ-5D-5L: EuroQOL Group 5-Dimension Health-related Quality of Life Measurement
FACIT-Pal: Functional Assessment of Chronic Illness Therapy Palliative
FAMCARE: Family Satisfaction with End-of-Life Care
ICER: Incremental cost-effectiveness ratio
IPOS: Integrated Palliative Care Outcomes Scale
MCID: Minimal clinically important difference
NCCS: National Cancer Centre of Singapore
QALY: Quality-adjusted life year
QoL: Quality of life
REDCap: Research Electronic Data Capture
SCQOLS: Singapore Caregiver Quality of Life Scale
SD: Standard deviation
U.S.: United States
